#### Statistical analysis

Differences in baseline characteristics of APOSTEL 8 follow-up participants will be compared between atosiban and placebo group using unpaired t-test, Mann-Whitney U test, χ^2^ test or Fisher’s exact test when appropriate. A two‐sided p<0.05 will be considered statistically significant. To detect potential attrition bias, baseline characteristics of follow-up participants will be compared with those lost to follow-up.

For the main outcomes, neurodevelopment and behaviour, we will report mean scores with SD and dichotomous outcomes (abnormal/mildly abnormal) of the domains and total score of the ASQ-3, Vineland screener and SDQ. For general health-related outcomes, we will report on the outcomes as previously described. For the outcome mortality, the denominator needs to be changed into all children born to participants of the original APOSTEL 8 trial.

For the main analysis, all outcomes will be analysed using generalised linear mixed effects model to enable accounting for the dependence of multiple pregnancies. For continuous outcomes, this will provide mean difference with 95% CI and for dichotomous outcomes OR with 95% CI. All analyses will be performed according to the intention-to-treat principle and complete case analysis using SPSS or R (latest version).

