## Methods and analysis

### Study setting

This study will be a follow-up study of the APOSTEL 8 study, an international, multicentre, randomised, double-blinded, placebo-controlled trial performed across 30 hospitals situated in the Netherlands, UK and Ireland (NL61439.018.17, EudraCT-number 2017-001007-72). The APOSTEL 8 trial includes women with threatened preterm birth between 30 and 34 weeks of gestation. Threatened preterm birth is defined as uterine contractions with (1) a cervical length <15 mm; (2) a cervical length of 15–30 mm with a positive fetal fibronectin test; or (3) a positive fibronectin test or insulin-like growth factor binding protein-1 (Actim-Partus test) in centres where cervical length measurement is not part of local protocol or (4) ruptured membranes. Eligible women are randomised to atosiban or placebo (0.9% saline) for 48 hours. The primary outcome is a composite of adverse perinatal outcomes including perinatal mortality and six severe perinatal morbidities: bronchopulmonary, periventricular leukomalacia >grade 1, intraventricular haemorrhage >grade 2, necrotising enterocolitis ≥stage 2, retinopathy of prematurity >grade 2 or needing laser therapy, andculture-proven sepsis. Secondary outcomes include various infant and maternal outcomes which can be found in the published protocol. The APOSTEL 8 started in 2017 and complete recruitment in 2023. Long-term follow-up of the APOSTEL 8 study was announced in the original trial protocol.^13^ This long-term follow-up study is directed at the children born to mothers who participated in the APOSTEL 8 trial, therefore, either exposed to atosiban or placebo during pregnancy. We will use four parent-reported questionnaires to assess neurodevelopment, behaviour problems and general health. Data collected in the original trial will be linked to the data obtained in this follow-up study. The study protocol has been developed according to the Standard Protocol Items: Recommendations for Interventional Trials criteria.

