### Sample size

The original APOSTEL 8 superiority trial with an aimed sample size of 760 pregnancies (of which approximately 635 singletons and 125 multiples). Since only participants of the original APOSTEL 8 trial are eligible for inclusion in this follow-up study, the maximum number of possible participants is fixed. Based on our previous follow-up studies using questionnaires, we expect to realise a follow-up rate of 50%,^20 22 36^ resulting in approximately 400 children to be included. Group sample sizes of 200 children in the atosiban group and 200 children in the placebo group achieve 80% power to detect a difference of 12% between group proportions in our composite main outcome. The test statistic used is the two-sided Z-Test with pooled variance with a significance level of the test is 0.05.

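### At the expected 50% follow-up, no stated analysis uses the linked baseline data to reduce non-response bias, and the responder versus lost-to-follow-up comparison is not specified by arm

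*Protocol article*

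**What the plan says.** All statements are in the protocol article.

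- **Follow-up (Sample size).** The article states "we expect to realise a follow-up rate of 50" per cent. It plans on "Group sample sizes of 200 children in the atosiban group and 200 children in the placebo group", which are said to "achieve 80% power to detect a difference of 12% between group proportions in our composite main outcome".
- **Main model (Statistical analysis).** A generalised linear mixed model is chosen so that children from the same multiple pregnancy are not treated as independent. All analyses are run "according to the intention-to-treat principle and complete case analysis". No baseline covariate is named, and none is excluded.
- **Two baseline comparisons (Statistical analysis).** The first is between arms among responders: "Differences in baseline characteristics of APOSTEL 8 follow-up participants will be compared between atosiban and placebo group". The second is offered as the attrition check: "To detect potential attrition bias, baseline characteristics of follow-up participants will be compared with those lost to follow-up". The second does not mention arm.
- **Missing outcomes (Additional sensitivity analyses).** Multiple imputation is used only if a missing-at-random assumption is tenable and follow-up exceeds 70%. Below that, best-case and worst-case scenarios are used.
- **Available data (Study setting).** "Data collected in the original trial will be linked to the data obtained in this follow-up study".

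**The concern.** Randomisation protects the comparison of all children born in the trial. It does not automatically protect the comparison of the half who respond. If response is related to prognosis differently in the two arms, the responding groups differ at baseline and the treatment contrast is biased. Labelling a complete-case analysis as intention-to-treat does not change that.

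The trial already holds baseline information that could be used against this. Plurality, membrane status and previous preterm birth are planned subgroup factors, and gestational age is an entry criterion. At the follow-up rate the article itself expects, though, the one named method that could use such data for non-responders (multiple imputation) is switched off, and the main model is described only in terms of clustering.

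The sentence presented as the attrition check compares those seen with those lost. If the arms are pooled, that shows whether the sample is representative. It does not show whether selection differed by arm, and that difference is what biases the contrast examined here.

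**Working it through.** **1. The plan's own figure.** The inputs are 200 per arm, a 12-point difference and a "two-sided Z-Test with pooled variance with a significance level of the test is 0.05". The base rate is not stated. With p̄ the mean of p1 and p2,

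power = Φ{ [ |p1 − p2| − 1.96·√(2·p̄(1 − p̄)/n) ] / √([p1(1 − p1) + p2(1 − p2)]/n) }.

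- 18% v 30%: (0.12 − 1.96 × 0.0427)/0.0423 = 0.86, so power is 80.5%.
- 20% v 32%: power is 78.3%.
- 30% v 42%: power is 70.7%.

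The stated 80% is reproduced for a lower rate of about 18% to 20%. This does not decide the present point. It fixes the scale: 12 points is the difference of interest.

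**2. What the fallback analyses can show at 50% follow-up.** Let the observed abnormal rate be p in both arms, with half of each arm missing. If all missing children in one arm are counted as abnormal and all in the other as normal, the difference is (0.5p + 0.5) − 0.5p = 0.50, whatever p is. Reversing the roles gives −0.50. The range is −50 to +50 points. If responders differed by the full 12 points, the range would be 0.5 × 12 ± 50, that is −44 to +56 points.

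**3. Selection on a measured factor, with no true effect.** These inputs are assumptions for illustration: a binary prognostic factor X with prevalence 40%, risk of an abnormal outcome 40% with X and 20% without, and overall response 50% in each arm. In arm A, children with X respond more often than those without by d. In arm B they respond less often by d.

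For d = 10 points, response is 56% (X) and 46% (no X) in arm A, and 44% and 54% in arm B.

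- Share with X among responders: A = 0.40 × 0.56/0.50 = 44.8%; B = 0.40 × 0.44/0.50 = 35.2%.
- Observed abnormal rate = 0.20 + 0.20 × share: A = 28.96%; B = 27.04%.
- False difference = 1.9 points, OR 1.10.

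For d = 20 points, response is 62% and 42% in A, and 38% and 58% in B. The shares are 49.6% and 30.4%, and the abnormal rates are 29.92% and 26.08%. The false difference is 3.8 points, OR 1.21.

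**4. What each check shows in these two cases.**

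| Check | d = 10 | d = 20 |
|---|---|---|
| Responders v lost, arms pooled (share with X) | 40% v 40% | 40% v 40% |
| Responders v lost within arm A | 44.8% v 35.2% | 49.6% v 30.4% |
| Responders v lost within arm B | 35.2% v 44.8% | 30.4% v 49.6% |
| Responders, A v B (planned) | 44.8% v 35.2% | 49.6% v 30.4% |
| Power of the planned A v B test, 200 per arm | 50% | 98% |

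The pooled table shows nothing in either case. The planned between-arm comparison finds the larger pattern reliably and the smaller one half the time.

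**5. Effect of adjustment.** Within each level of X the two arms have the same risk (40% or 20%), so adjusting for X removes the 1.9 or 3.8 points entirely. This holds by construction, because here selection runs only through X.

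**The case against.** The strongest reply has four parts.

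*The plan does look by arm.* A reader might infer from the attrition sentence that differential selection could not be detected. The documents do not support that. The between-arm comparison of responders is an arm-specific check, because randomisation balances the full cohort and imbalance among responders on measured factors therefore signals selection. This part stands. What remains is limited power for modest selection, no stated consequence if imbalance is found, and no mention of arm in the second comparison.

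*Silence is not exclusion.* A reader might also infer that the model is fixed as unadjusted. The article does not say so. A covariate list may sit in a full protocol or SAP that is not shown. This stands as far as the model formula goes. But the article does fix the missing-data rule, and under that rule its own expected follow-up leaves only the scenario bounds.

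*Missingness is addressed.* Best-case and worst-case analyses are planned and should be credited. At 50% follow-up they cannot distinguish serious bias from none.

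*Blinding is retained.* Parents do not know the allocation until participation is complete, so knowledge of treatment should not drive response. This lowers the risk but does not abolish it: if treatment alters the neonatal course and that course affects willingness to respond, selection can differ by arm under full blinding.

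A larger bias figure is also tempting. With a true 30% rate and 50% response in both arms, suppose families of abnormal children respond at 60% in one arm and 50% in the other. The observed rates are then 0.30 × 0.60/0.50 = 36% v 30%, a false 6 points. That is selection on the 4-year outcome itself. Baseline adjustment need not remove any of it, so the 6 points cannot be attributed to missing adjustment.

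**Conclusion.** The point holds in a limited form. At the expected 50% follow-up the article states no analysis that uses the linked baseline data to reduce non-response bias or to gain efficiency, and its responder versus lost-to-follow-up comparison is not specified by arm.

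The size is uncertain, because the document gives neither predictor strengths nor response patterns. Under the stated assumptions (one factor, prevalence 40%, risks 40% and 20%, opposite response gaps of 10 or 20 points), the bias is 1.9 to 3.8 points, roughly one sixth to one third of the 12-point target. Weaker predictors, or selection in the same direction in both arms, would give less. The efficiency gain from adjustment is not quantified here.

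This is a worthwhile improvement to a workable plan. It does not show that the comparison will be biased.

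**What to change.** - **Main model.** Pre-specify adjustment for a short list of prognostic factors fixed before randomisation: gestational age at randomisation, singleton or multiple, membrane status and previous preterm birth. Keep the unadjusted result as supportive. If a SAP already lists covariates, align the two documents.
- **Effect measure.** The adjusted OR is conditional on the covariates, so report a standardised risk difference with its confidence interval beside it.
- **Attrition reporting.** Give response rates by arm, and compare responders with non-responders within each arm. Include the original trial's neonatal outcome in these tables descriptively. It arises after randomisation and may lie on the treatment pathway, so it should not be a covariate in the main model.
- **Limits.** State that adjustment addresses only selection through the measured factors, and not response that depends on the child's condition at 4 years.

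The cost is wording. Three of the four factors are already planned subgroup variables and gestational age is part of trial entry. The article already presupposes baseline data on those lost to follow-up, so no new data collection is needed. The list should be fixed before outcome data are seen by arm, so that covariates are not chosen in response to observed imbalance.

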Besides the effects on the immediate neonatal period before hospital discharge, it is essential to extend our scope on long-term child’s health and developmental outcomes since pregnancy interventions can have unexpected harmful long-term effects.^14^,^18^ However, thus far only a few randomised trials concerning tocolytic drug administration during pregnancy have performed long-term follow-up on child development. Our research group conducted the APOSTEL II trial, comparing nifedipine maintenance therapy to placebo in case of threatened preterm birth between 26 and 32 weeks of gestation.^19^ At 2 years of age, we found a higher rate of fine motor problems in the nifedipine group (n=78) (22.2% vs 7.6%), but lower rate of poor problem-solving (21.2% vs 29.1%) compared with the placebo group (n=66).^20^ We concluded that there was insufficient evidence to support use of nifedipine for maintenance tocolysis. Second, the APOSTEL III trial compared tocolysis with nifedipine versus atosiban in threatened preterm birth between 25 and 34 weeks of gestation.^21^ Follow-up at 2.5–5.5 years showed composite abnormal development in 30% of children in the nifedipine group (n=115) and 38% in the atosiban group (n=110).^22^ Neither nifedipine nor atosiban was considered as preferred treatment in women with threatened preterm birth on both short-term and long-term outcome. A recent population-based cohort study including 600 children reported no difference in neurodevelopmental outcomes at 5.5 years among children with and without antenatal exposure to tocolysis by atosiban or nifedipine. However, follow-up outcomes were retrospectively obtained and the population solely concerned pregnancies complicated by preterm prelabor rupture of membranes between 24 and 32 weeks gestation.^23^

In conclusion, long-term effects of tocolytic drug administration during pregnancy on child outcomes are still largely unknown. We will, therefore, perform a follow-up study of the randomised placebo-controlled APOSTEL 8 trial. This follow-up study aims to determine the long-term effects of atosiban versus placebo in threatened preterm birth on neurodevelopment, behaviour problems and general health of children around 4 years of corrected age. The APOSTEL 8 follow-up will help to identify potential beneficial or harmful effects of atosiban administration during pregnancy and will contribute to further improving threatened preterm birth healthcare.

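### The analysis section spreads the label of main outcome over all domain and total scores of three questionnaires, while the sample size powers a single composite that this section does not name

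*Protocol article*

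**What the plan says.** The protocol article describes its leading outcome differently in different places.

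- **Abstract, Methods and analysis:** two constructs, neurodevelopment and behaviour problems, are primary. No composite is mentioned.
- **Outcomes, including Table 1:** the primary outcomes, in the plural, include a composite over the ASQ-3, Vineland screener and SDQ. The table splits it into abnormal and mildly abnormal. Outcomes are also to be reported separately.
- **Composite outcomes:** three composites are listed: abnormal, mildly abnormal, and death or abnormal survival.
- **Sample size:** 200 children per arm "achieve 80% power to detect a difference of 12% between group proportions in our composite main outcome". The level is fixed as well: "The test statistic used is the two-sided Z-Test with pooled variance with a significance level of the test is 0.05".
- **Statistical analysis:** under the two constructs, here called the main outcomes, "we will report mean scores with SD and dichotomous outcomes (abnormal/mildly abnormal) of the domains and total score of the ASQ-3, Vineland screener and SDQ". The composite is not named. Then: "For the main analysis, all outcomes will be analysed using generalised linear mixed effects model". Results are mean differences or odds ratios with 95% confidence intervals.

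The Statistical analysis section has one sentence on significance: "A two‐sided p<0.05 will be considered statistically significant". It stands between the sentence on baseline comparisons and the sentence on attrition, and it is not expressly limited to either.

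**The concern.** The 5% error rate behind the sample size belongs to one comparison. The analysis section attaches the label of main outcome to two constructs and expresses them through many scores, each in several forms. A report that follows this section could present any of them as a main result, and an unadjusted 95% interval that excludes the null amounts to the same 5% decision. With that many comparisons, a nominally significant result somewhere is likely even if atosiban does nothing.

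This matters because the Background says the follow-up should help identify possible benefit or harm of atosiban. The same section shows that single domains get attention. Of the earlier nifedipine follow-up it says "we found a higher rate of fine motor problems in the nifedipine group (n=78) (22.2% vs 7.6%), but lower rate of poor problem-solving". An isolated domain difference in this study could be put forward as a main finding when it is chance.

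**Working it through.** **1. The plan's own figure.** The stated 80% power uses a two-sided pooled Z-test, α = 0.05, n = 200 per arm and a difference of 12 points. The base rate is not given. For 18% vs 30%:

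- pooled rate 0.24; SE under the null = √(2 × 0.24 × 0.76 / 200) = 0.0427
- SE under the alternative = √((0.18 × 0.82 + 0.30 × 0.70) / 200) = 0.0423
- power = Φ((0.12 − 1.96 × 0.0427) / 0.0423) = Φ(0.858) ≈ 80.5%

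The figure reproduces when the lower rate is about 17–20%. It describes one test of one composite.

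**2. Counting what the analysis section covers.**

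| Instrument | Domains | Total defined? | Cut-offs defined for |
|---|---|---|---|
| ASQ-3 | 5 | no | a rule across the domains (abnormal, mildly abnormal) |
| Vineland screener | 4 | yes | total (abnormal, mildly abnormal) |
| SDQ | 5 | yes, from four domains | total (abnormal, mildly abnormal) |

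Defined mean scores: 5 + (4 + 1) + (5 + 1) = 16. Defined dichotomies: 3 instruments × 2 = 6. Together there are 22 comparisons.

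The widest literal reading adds an ASQ-3 total and separate abnormal and mildly abnormal results on every scale: 17 × 3 = 51. The document does not define most of those dichotomies.

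**3. Ceiling under independence.** 1 − 0.95^k gives 56% for k = 16, 68% for k = 22 and 93% for k = 51. The scores are not independent: totals are sums of domains, and dichotomies are functions of the same scores. These values are therefore too high.

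**4. Simulation under no effect.** Assumptions:

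- 200 independent children per arm; clustering of multiples is ignored
- 14 multivariate normal domain scores, with totals as sums (SDQ total from four domains)
- t-tests on means and pooled Z-tests on dichotomies, each at 0.05
- within/between-instrument correlations assumed at 0.3/0.2, 0.5/0.4 and 0.7/0.5

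Chance of at least one p < 0.05:

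| Set | 0.3/0.2 | 0.5/0.4 | 0.7/0.5 |
|---|---|---|---|
| 17 means (with an ASQ-3 total) | 49% | 38% | 31% |
| 17 means + 6 defined dichotomies | 59% | 50% | 44% |
| 51 comparisons | 87% | 82% | 79% |

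The undefined ASQ-3 total hardly matters. With defined scores only, the 16 means give about 32–49%, and the 16 means plus 6 dichotomies about 44–59%. A repeat of the defined-scores set with 4,000 replicates gave 46%, 38% and 30% for the 16 means and 57%, 51% and 44% for all 22, which agrees to within about three points. An intermediate set of 34 comparisons (17 means plus one dichotomy each) gives 54–72% over a similar range of correlations.

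**5. With one composite named.** The chance is 5% by construction. Two composites tested at 0.05 each would give 1 − 0.95² = 9.8%, and all three listed composites 1 − 0.95³ = 14.3%, if they were independent. The confirmatory outcome therefore has to be one composite, not the group of them.

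**The case against.** The strongest reply is that the primary outcome is set elsewhere. Table 1 has a primary-outcome row that defines a composite, and the Sample size section powers that composite at 0.05. The analysis section names two constructs and lists scores to report under them. Its phrase about the main analysis covers all outcomes, general health included, so it names the model rather than giving each score confirmatory status. The sentence on p<0.05 stands among baseline and attrition comparisons, and treatment effects are described by confidence intervals.

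Much of this stands, and it rules out some stronger readings.

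- A reader might infer that every domain score is a primary endpoint formally judged at p<0.05. The text does not say so.
- A reader might infer a false-positive chance of about 80%. That needs the 51 comparisons, most of whose dichotomies have no stated cut-off.
- A reader might take the Background as proof that the group claims effects from isolated domains. The conclusion drawn there was that evidence for nifedipine maintenance was insufficient.

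It is also fair that a multiplicity rule may sit in an analysis plan that is not shown. Its absence is not the point made here.

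What the reply does not remove is the conflict within the article. The abstract and the analysis section give the leading role to two constructs, the analysis section expresses them as a long list of scores without mentioning the composite, and the sample size rests on the composite alone. An analysis plan written to match the analysis section would inherit the conflict.

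**Conclusion.** The point holds as an inconsistency of status with a measurable consequence. The article powers one composite at two-sided 0.05, but its analysis section applies the label of main outcome to a family of component results with unadjusted intervals and does not single out the composite.

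Under no effect, some nominally significant main result has a chance of about 44–59% on the 22 defined comparisons and about 32–49% on the means alone, against a nominal 5%. It reaches 79–87% only if abnormal and mildly abnormal are tested separately on every scale. All of these figures depend on assumed correlations, normal scores and independent children. The conclusion does not turn on the exact value, since the lowest is still about six times the nominal level.

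**What to change.** In the abstract and the Statistical analysis section, name the one composite that the Sample size section powers as the single confirmatory outcome, say which of the listed composites it is, and tie the two-sided 0.05 criterion to it. Label the domain, total, mean and mildly abnormal results secondary or supportive. Report them as estimates with 95% confidence intervals, without a significance claim, and state how many comparisons were made. If claims at instrument level are wanted, a short adjusted sequence after the composite is possible but optional.

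The cost is a few sentences and no new data. The small downside is that an isolated domain difference can no longer be called a significant main finding. Its estimate and interval stay visible as a signal.

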### Participants/eligibility criteria

Children of both singleton and multiple pregnancies, born to mothers who participated in the APOSTEL 8 trial, will be eligible for inclusion. Assessment will be performed when children are around 4 years of corrected age (ideally between 3 years and 9 months (3;9) to 4 years and 3 months (4;3) years of corrected age). Participants who did not give consent to be approached for follow-up research in the original APOSTEL 8 trial, will not be approached in this follow-up study. Also, participants included in the UK or Ireland will not be eligible for inclusion.

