### Study design

The APOSTEL 8 follow-up study will be performed within the Dutch consortium for Healthcare Evaluation and Research in Obstetrics and Gynaecology (NVOG Consortium; https://zorgevaluatienederland.nl/NVOG). Good clinical practice trained researchers from the Amsterdam University Medical Center will cross-check medical records and Dutch Personal Record database of both mother and child(ren) for the possible occurrence of death. Thereafter, information letters and informed consent forms of this follow-up study will be sent by email to the APOSTEL 8 participants. Contact details of the research team are shared in the information letter to facilitate the opportunity to ask potential questions or discuss concerns. If the email address is unknown, participants will be contacted by phone and informed consent forms will be sent by mail. After giving informed consent, participants are redirected to the online questionnaire via a web link. Participants can withdraw participation at any time.

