#### Mortality

Child death (defined as perinatal mortality and death up to 4 years of corrected age). Medical records and the Dutch Personal Records Database will be used to verify the number of deceased children.

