#### Additional sensitivity analyses

In accordance with the APOSTEL 8 trial, the following subgroup analyses are planned:

Singleton and multiple pregnancy separately.Cervical length <15 mm vs cervical length 15–30 mm and a positive fibronectin test (or no

cervical length measurement and a positive fibronectin test or Partus test).

Ruptured vs intact membranes at entry.Previous preterm birth.Excluding children that exceed the optimal window of 3;9 years–4;3 years of corrected age. In sensitivity analyses, we will use imputation techniques to impute missing outcome data for children lost to follow-up. Multiple imputation techniques will only be applied when it can be assumed that data are missing at random and the follow rate is >70%. the follow-up rate is lower than 70, a best-case and worst-case scenario analyses will be performed.Composite outcome of deceased children or survived children with abnormal cognitive and/or behaviour development. Combining mortality data with survival of children with a severe developmental disability will help in providing the full scope of relevant outcomes from the start of randomisation until up to 4 years of age. The denominator in this analyses will be all children born in the APOSTEL 8 trial, instead of the number of children included in follow-up. However, this outcome has some challenges due to the high probability of loss to follow-up (as is the case in many obstetrical follow-up studies after several years), and therefore, the inevitable need to deal with missing data. This will be done by either applying multiple imputation techniques or, in case of a high loss to follow-up, a worst-case and best-case scenario analyses.

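### Mortality and the death-or-abnormal composite are divided by all children of the three-country trial, although UK and Irish children are excluded from follow-up and the only death register named is Dutch

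*Protocol article*

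**What the plan says.** All references are to the protocol article.

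- **Where the trial ran.** Study setting describes a trial "performed across 30 hospitals situated in the Netherlands, UK and Ireland".
- **Who is followed up.** Participants/eligibility criteria says that "participants included in the UK or Ireland will not be eligible for inclusion".
- **How deaths are found.** Under Study design, researchers of one Dutch centre "will cross-check medical records and Dutch Personal Record database of both mother and child(ren) for the possible occurrence of death". The Mortality section repeats this: "Medical records and the Dutch Personal Records Database will be used to verify the number of deceased children". The outcome runs from the perinatal period to 4 years of corrected age.
- **Denominator for mortality.** Statistical analysis: "For the outcome mortality, the denominator needs to be changed into all children born to participants of the original APOSTEL 8 trial". The notes to Table 1 say the same.
- **Denominator for death or survival with abnormal development.** Additional sensitivity analyses: "The denominator in this analyses will be all children born in the APOSTEL 8 trial, instead of the number of children included in follow-up".
- **Missing outcomes.** The same section allows multiple imputation only if data can be assumed missing at random and follow-up exceeds 70%. Otherwise it calls for best-case and worst-case analyses.

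No section limits either denominator to Dutch participants.

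**The concern.** The children in whom an event can be found are not the children the events are divided by.

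For mortality, no described search reaches a UK or Irish child who died after the original trial's data collection. That child would stay in the denominator and be counted as alive, so the later-death percentage would be too low.

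For the composite, surviving UK and Irish children have no ASQ-3, Vineland or SDQ result because nobody plans to ask for one. The section attributes the missing data to loss to follow-up and does not mention this group. These children add to the missing share, and any imputation for them would extrapolate to countries with no observed questionnaires. They can enter the composite with an observed outcome only as deaths, never as assessed survivors.

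**Working it through.** **Inputs from the article.** The target was 760 pregnancies, about 635 singletons and 125 multiples; the expected follow-up rate is 50%, giving about 400 children (all from Sample size). The imputation threshold is 70% (Additional sensitivity analyses).

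**Assumptions.** The UK/Irish share of children, *f*, is not given, so I take 5%, 10% and 20%. All multiples are taken as twins. The number of children in the whole trial is then 635 + 2 × 125 = 885.

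**The plan's own figure.** 50% of 760 is 380 and 50% of 885 is 442.5, so about 400 lies between the two. As a share of 885 children, 400 is 45%. The article does not say whether the 50% refers to all participants or to eligible Dutch ones, so both readings are shown below. The 80% power figure concerns the questionnaire composite and does not enter this point.

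**1. Later mortality.** If no later deaths are found outside the Netherlands, reported rate = true rate × (1 − *f*). With an assumed true later-death rate of 1.0%:

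| *f* | Dutch children, 885 × (1 − *f*) | Reported later-death rate |
|---|---|---|
| 5% | about 841 | 0.95% |
| 10% | about 796 | 0.90% |
| 20% | 708 | 0.80% |

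The relative understatement equals *f*, whatever the true rate.

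**2. Total mortality.** The outcome also includes perinatal deaths. Study setting says original trial data will be linked, so these can be obtained for all three countries. If later deaths are a fraction *q* of all deaths, the relative dilution of total mortality is *q* × *f*. With an assumed *q* of 25%, this is 0.25 × 5% = 1.25% up to 0.25 × 20% = 5%.

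**3. Odds ratio.** Suppose later-death rates of 1% and 2% in the two arms and *f* = 20% in both. The true odds ratio is (0.02/0.98)/(0.01/0.99) = 2.02. After dilution to 0.8% and 1.6% it is (0.016/0.984)/(0.008/0.992) = 2.02. The comparison hardly moves.

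**4. Missing share in the composite** (ignoring the few children whose outcome is known through death).

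- *If 50% of Dutch children respond:* the Dutch denominator gives 50% missing. The whole-trial denominator gives 1 − 0.5 × (1 − *f*) = 52.5%, 55% and 60%.
- *If 400 children respond in any case:* the whole-trial denominator gives 1 − 400/885 = 54.8% missing. The Dutch denominator gives 1 − 400/841 = 52.4%, 1 − 400/796 = 49.7% and 1 − 400/708 = 43.5%.

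Under either reading the whole-trial denominator has the larger missing share.

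**5. Best-case and worst-case bounds.** Let both arms have observed rate *p* and missing share *m*. Setting all missing children to abnormal in one arm and normal in the other gives a risk difference of [*p*(1 − *m*) + *m*] − *p*(1 − *m*) = *m*. Under the first reading in step 4, the bounds go from ±50 points to ±52.5, ±55 and ±60 points.

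**6. The 70% threshold.** If follow-up is counted over all children, 70% response among Dutch children becomes 0.70 × (1 − *f*) = 66.5%, 63% and 56%. The condition for multiple imputation would fail through the country exclusion alone.

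**The case against.** - **The main analysis is untouched.** This stands. The composite behind the sample size rests on questionnaires and is analysed in complete cases. Table 1 lists mortality among the measures of the primary outcome, but its definitions of abnormal and mildly abnormal contain no death. The composite that includes death is placed among the sensitivity analyses.
- **The treatment effect is not biased in any material way.** A reader might infer that the mortality odds ratio is distorted. The documents do not support that: allocation is randomised and blinded, missed deaths would affect both arms, and step 3 shows almost no change when countries are balanced and later deaths are rare.
- **UK and Irish deaths may not be missed at all.** The article does not restrict medical records to Dutch ones. This stands as far as it goes, so it cannot be said that later deaths there will be missed. But no access to such records is described, and access would not supply questionnaire outcomes for the composite.
- **The sizes are soft.** This stands. The country share is assumed, and the 50% response need not refer to Dutch children. Opposite-extreme bounds are one reading of best and worst case; setting missing children the same way in both arms would not widen the difference. Bounds of ±50 points are uninformative already, and at the expected 50% response the 70% threshold is not met anyway.
- **The wide denominator has a purpose.** The article wants the full picture from randomisation onwards. Restriction by country does not break the randomised comparison, because country is fixed before randomisation. That argument does not cover restricting to children whose vital status can be verified, so such a condition should not define the denominator.

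**Conclusion.** The concern holds as an inconsistency between the denominators and the population that is followed up. As written, later deaths are divided by children for whom no means of tracing is described, and the composite counts as missing a group that was never to be assessed. What suffers is the absolute later-death percentage and the composite's missing-data analysis.

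The size is illustrative only. With an assumed UK/Irish share of 5–20%, and no later deaths found there, the later-death component is 5–20% too low in relative terms, and total mortality by less. If 50% of Dutch children respond, the composite's missing share rises from 50% to 52.5–60%. The mismatch itself exists for any share above zero.

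This should be fixed before analysis, but it does not threaten the trial's main conclusion.

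**What to change.** 1. Define the denominator for mortality to 4 years, and for death or survival with abnormal development, as all children born to participants randomised in the Netherlands, whether or not questionnaires were returned.
2. Report any child whose vital status cannot be checked as missing, not as a survivor.
3. Report perinatal deaths for the whole trial separately, from the linked trial data.
4. Make the change in Statistical analysis, in Additional sensitivity analyses and in the Table 1 notes. State there that the follow-up rate compared with 70% is counted over the same Dutch denominator.

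For mortality only, an alternative is to keep the whole-trial denominator and name the source of 4-year vital status for UK and Irish children. This does not help the composite, whose questionnaire outcomes would still be absent for those children.

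The cost is wording in three places and a smaller denominator: about 708 to 841 children instead of 885 under the assumed shares. No new data are needed for the main option.
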